**Self-rated symptoms**					
	AUDIT^d^	Alcohol consumption	Interval		0-40
	GAD-7^e^	Anxiety symptoms	Interval		0-21
	SMBQ^f^ cognitive weariness	Burnout	Continuous		0-7
	SMBQ exhaustion	Burnout	Continuous		0-7
	SMBQ listlessness	Burnout	Continuous		0-7
	MADRS-S^g^	Depression	Interval		0-54
	KEDS^h^	Exhaustion disorder	Interval		0-54
	WHODAS^i^ 2.0	Functional disability	Continuous		0%-100%
	EQ-5D-5L	Quality of Life	Interval		5-25
	BBQ^j^	Quality of life	Interval		0-96
	ISI^k^	Insomnia severity	Interval		0-28
	SRH-5^l^	Self-rated health	Interval		0-5
	PSS-10^m^	Perceived stress	Interval		0-40
	PHQ-15^n^	Somatoform symptoms	Interval		0-30
	6-QEMP^o^	Subjective memory impairment	Interval		0-30
**3-week measurement**					
	SMBQ cognitive weariness	Burnout	Continuous		0-7
	SMBQ exhaustion	Burnout	Continuous		0-7
	SMBQ listlessness	Burnout	Continuous		0-7
	ISI	Insomnia severity	Interval		0-28
	PSS-10	Perceived stress	Interval		0-40
**Treatment-related predictors**					
	Clinician treatment expectancy	—	Interval	✓	0-10
	Treatment credibility scale	—	Interval		0-10
**Cognitive functioning**					
	SDMT^p^	Attention and processing speed	Interval		0-∞
	FAS^q^	Executive functions	Interval		0-∞
	Stroop index	Executive functions	Continuous		0-∞
	Stroop inhibition	Executive functions	Continuous		0-∞
	CERAD^r^ learning	Memory	Interval		0-30
	CERAD recognition	Memory	Interval		0-10
	Corsi forward	Memory	Interval		0-9

^a^Not applicable.

^b^S-ED: self-rated exhaustion disorder.

^c^ADNM-8: The Adjustment Disorder New Module-8.

^d^AUDIT: Alcohol Use Disorder Identification Test.

^e^GAD-7: General Anxiety Disorder-7.

^f^SMBQ: Shirom-Melamed Burnout Questionnaire.

^g^MADRS-S: Montgomery-Åsberg Depression Rating Scale.

^h^KEDS: Karolinska Exhaustion Disorder Scale.

^i^WHODAS: World Health Organization Disability Assessment Schedule.

^j^BBQ: Brunnsviken Brief Quality of Life Scale.

^k^ISI: Insomnia Severity Index.

^l^SRH-5: Self-Rated Health-5.

^m^PSS-10: Perceived Stress Scale-10.

^n^PHQ-15: Patient Health Questionnaire-15.

^o^6-QEMP: 6-item Questionnaire of Everyday Memory Problems.

^p^SDMT: Symbol Digit Modality Test.

^q^FAS: Verbal Fluency Test.

^r^CERAD: Consortium to Establish a Registry for Alzheimer’s Disease.

#### Sociodemographic Variables

Information on age (interval), sex (male, female, other, or prefer not to disclose), relationship status (in relationship, single, or widowed), number of children, educational attainment (in 9 categories between <9 years of school to PhD), employment status (eg, student, unemployed, or full-time work), and employment type (in 11 categories, eg, employed in the private sector, by the municipality, or other) was gathered before the start of treatment using the web-based study platform. Self-rated reading and computer skills were rated separately on a 5-step ordinal scale from *poor* to *very good*. Patients also reported if they were Swedish native speakers.

#### Clinical Characteristics

During the clinical interview, patients reported their medication regimen, specifying both the number (0-4) and type of medication (antidepressants, anxiolytics, sleep medication, and pain medication and yes or no). Primary diagnosis (AD or ED), and possible secondary psychiatric diagnosis (eg, anxiety or depressive disorder) was assessed by the clinician using Mini International Neuropsychiatric Interview, self-rated ED (ordinal categories ranging from *no* to *yes—to a high degree*) [32], and the ADNM-8 [33]. Using ADNM-8, the patient was asked about which specific stressors had been present in the past 2 years (in 16 options, eg, *too much or too little work* or *financial difficulties*). The clinician assessed the length of the current episode (in months), and the age of the patients first episode (in years). Sick-leave status upon inclusion in the study (0%-100% in 5 steps), length of current sick-leave episode (*0-1 months* to *>12 months* in 5 categories) was self-reported.

#### Self-Rated Symptoms

*Alcohol use* was assessed using the Alcohol Use Disorder Identification Test [40,41]. This 10-item screening instrument evaluates alcohol consumption, drinking behavior, and alcohol-related problems over the past year. It contains items, such as *How often do you have six or more drinks on one occasion*? rated on various ordinal scales, typically ranging from 0 to 4.

*Symptoms of anxiety* were measured using the Generalized Anxiety Disorder-7 scale [42]. This screening tool assesses generalized anxiety symptoms over the past 2 weeks. It comprises 7 items, such as *not being able to stop or control worrying* rated on a 4-point ordinal scale ranging from 0 *not at all* to 3 *nearly every day*.

*Symptoms of burnout* were measured using the Shirom-Melamed Burnout Questionnaire [43,44]. It aims to measure 3 components of burnout; emotional and physical fatigue, cognitive weariness, and listlessness and contains statements such as *I have difficulty concentrating* rated on a 7-point scale ranging from 1 *never or almost never* to 7 *always or almost always* with some items using reversed scoring.

*Symptoms of depression* were measured using Montgomery-Åsberg Depression Rating Scale [45]. It is a 9-item questionnaire used to measure different aspects of depression such as concentration difficulties, suicidal thoughts, sadness, and affected appetite with answers rated on a 7-point ordinal scale from 0 to 6.

*Symptoms of exhaustion disorder* were measured using the 9-item Karolinska Exhaustion Disorder Scale [46]. Measuring different aspects of exhaustion such as fatigue, endurance, and sleep impairment, answers are rated on an ordinal scale from 0 to 6 (eg, ability to concentrate; ranging from 0 “I do not have any difficulty concentrating, and can read, watch TV and converse normally” to 6 “I cannot concentrate on anything at all*.*”)

*Functional disability* was measured using The World Health Organization Disability Assessment Schedule (2.0) [47], developed to assess functioning in the last 30 days in 6 different life domains, including cognition, mobility, self-care, relationships, life activities, and societal participation. It contains statements, such as “I have difficulty standing for longer periods such as 30 minutes.” Answers are rated on a 5-point ordinal scale ranging from 0 *never* to 4 *extreme or unable*. A 12-item version was used.

*Quality of life* was assessed using the EQ-5D-5L [48,49] and the Brunnsviken Brief Quality of Life Scale [50]. The EQ-5D-5L contains 5 dimensions: mobility, self-care, usual activities, pain or discomfort, and anxiety or depression each rated on 5 levels of severity from *no problems* to *extreme problems*. The Brunnsviken Brief Quality of Life Scale is a 12-item questionnaire that assesses 6 life areas (leisure time, view on life, learning, creativity, view of self, and friends and friendship). Ratings range from 0 *strongly disagree*, to 4 *strongly agree*, on statements of the importance and satisfaction of each area.

*Insomnia severity* was measured using the Insomnia Severity Index [51]. The Insomnia Severity Index is a 7-item questionnaire designed to assess aspects of insomnia, including difficulty falling asleep, difficulty staying asleep, and satisfaction with sleep. Ratings are given using an ordinal scale ranging from 0 to 4.

*Self-rated health* was assessed using Self-Rated Health 5 asking patients to rate their general health on a scale of 1, *very bad* to 5 *very good* [52].

*Somatoform symptoms* were assessed using the Patient Health Questionnaire [53]*.* It consists of 15 questions covering somatic symptoms commonly seen in primary care, such as back pain, headache, and nausea. Answers are rated on a 3-point ordinal scale ranging from *not at all bothered* to *bothered a lot.*

*Subjective memory impairment* was measured using the 6-item Questionnaire of Everyday Memory Problems (6-QEMP) [54]. A 5-item version has previously been used to assess subjective memory problems in this patient population [55,56]. The present version was adapted by [name] for use in patients with stress-related disorders with statements, such as “How do you think your memory functions now compared to before your stress-related mental health problems?.” The answers are rated on a 5-point ordinal scale.

#### Treatment-Related Predictors

*Clinician Treatment Expectancy* was judged after patient assessment, upon inclusion in the study, by clinicians rating the probability of the patient improving after treatment on a scale of 0 *no improvement* to 10 *full remission*.

The *Treatment Credibility Scale* was administered 3 weeks after the start of treatment [57]. Patients were asked questions about their impression of the treatment and if they thought they would improve. It included statements such as “How logical do you think this treatment is?” and “How confidently would you recommend this treatment to a friend with the same problems as you?” on a scale of 0 *not at all* to 10 *very logical*, *very confidently.*

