### Objective of the Study

The overall objective of this study is to predict treatment outcomes in patients with stress-related disorders. Due to limitations in existing methods for prediction analyses, this study aims to first evaluate putative predictors using a traditional prediction paradigm, and second to model treatment outcomes using an ML approach. Our primary outcome of interest is responder status after treatment on the Perceived Stress Scale-10 (PSS-10), evaluated using the reliable change index (RCI; further described in the Planned Statistical Analysis and Data Cleaning and Preparation sections). On the basis of earlier research on predictors of treatment outcome, we hypothesize that key predictors will include younger age, education level, baseline symptom severity, treatment credibility, and history of sickness absence. Furthermore, we anticipate that the ML models will outperform a dummy model predicting the majority class and achieve a BACC of ≥67%, thus being indicated clinically useful [28].

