#### Treatment

Patients were randomized to one out of two 12-week internet-delivered treatments (CBT and general health-promoting advice). They both consisted of web-based text-based modules with related exercises and assignments. Patients were guided sequentially through the modules by a therapist via a secure web-based platform. The therapists’ primary role was to provide feedback on exercises, support in problem-solving, and to give emotional and technical support via weekly asynchronous text messages. Therapists were licensed clinical psychologists or clinical psychology students in their final year of training. Because this study will not evaluate the individual treatments, they will not be further described here. A full description of the treatments is described in the study by Sennerstam et al [34].

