### Outcomes

The primary outcome in this study and the original RCT is PSS-10 [35]. The PSS-10 is a self-report questionnaire developed to evaluate an individual’s perception of life as unpredictable, uncontrollable, and overwhelming. Responses are recorded on an ordinal scale ranging from 0 n*ever* to 4 *very often*, reflecting the individual’s feelings and thoughts over the past month. It contains statements, such as ‘*In the last month, how often have you been upset because of something that happened unexpectedly?’* and sum scores range from 0 to 40. The PSS is the most commonly used outcome measure of stress-management interventions globally [8,36,37]. For this study, a Swedish version of the PSS-10 was used. The PSS-10 has been found to exhibit high internal consistency (Cronbach α=0.84) and adequate construct validity [38]. The PSS-10 was administered digitally through the web-based study platform before randomization to treatment, every 3 weeks during the treatment phase, and at treatment completion (12 weeks). During treatment, the instructions for the PSS-10 were modified to have patients consider the last week instead of the last month. For this study, the sum score of the PSS-10 will be dichotomized into responder or nonresponder after treatment based on the RCI criteria [39] to differentiate between statistically significant change and those attributable to measurement error or natural variability. The PSS-10 baseline and 3-week measurement will also be used as predictors.

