#### Predictor Analysis

For the traditional regression analysis, data will be imputed using the KNN imputer. The imputer, a nonparametric imputation method, works by imputing missing values based on the k-nearest neighbors; in this study *k* will be determined by cross-validation. It uses the Euclidean distance metric to find the nearest neighbors and can be used for both numerical and categorical data. Each missing value is imputed using values from its k-nearest neighbors. After imputation, we will run univariate logistic regressions for each predictor listed in Table 1 using RCI as a target variable. Predictors that are statistically significant in the univariate analyses will then be included in an ablation study, a systematic approach to evaluate feature importance. This method involves iteratively removing each significant predictor from a full model, measuring the change in explained variance, and then reinserting it, thereby quantifying each predictor’s unique contribution to the model’s explanatory power in the context of all other features.

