### Comparison to Prior Work

To the best of our knowledge, this is the first study to apply an ML approach to study predictors of treatment outcome in patients diagnosed with AD or ED. In line with previous traditional prediction research of treatment outcomes in stress-related disorders, we hypothesize that younger age, education level, symptom severity, treatment credibility, and history of sickness absence will predict treatment response [15,22]. Furthermore, we anticipate that the ML models will outperform a dummy model and achieve a BACC of 67% or higher, surpassing the benchmark indicated by Forsell and others [28]. If confirmed, our findings would support the notion that predictive models using sociodemographic, clinical, self-rated, treatment-related, and potentially cognitive variables are valuable when predicting therapy outcomes, as have been suggested in other patient populations [17,18,80]. In subsequent research, these models should be externally validated and tested in implementation trials to assess their utility as decision support tools. Such trials could evaluate whether integrating predictions into treatment planning improves outcomes and supports personalized care.

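### Credibility is rated 3 weeks into treatment and tested without covariates, so a significant result cannot show a contribution beyond improvement already made

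*Protocol article*

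**What the plan says.** - **Hypothesis.** Objective of the Study: "we hypothesize that key predictors will include younger age, education level, baseline symptom severity, treatment credibility, and history of sickness absence". Comparison to Prior Work repeats that "symptom severity, treatment credibility, and history of sickness absence will predict treatment response".
- **Timing and content.** Treatment-Related Predictors says the Treatment Credibility Scale "was administered 3 weeks after the start of treatment [57". On content: "Patients were asked questions about their impression of the treatment and if they thought they would improve". The Treatment section gives the length: "Patients were randomized to one out of two 12-week internet-delivered treatments".
- **Outcome.** Under Data Cleaning and Preparation, response is a reliable change index computed on PSS-10 from before to after treatment, with a threshold of -1.96 and reliability 0.83.
- **Test.** Predictor Analysis: "we will run univariate logistic regressions for each predictor listed in Table 1 using RCI as a target variable". No covariates are named.
- **Second step.** Only predictors significant on their own go on to the ablation, described as "iteratively removing each significant predictor from a full model, measuring the change in explained variance, and then reinserting it". No test or decision rule is attached to the change in explained variance.
- **Early symptom scores.** Outcomes: "The PSS-10 baseline and 3-week measurement will also be used as predictors". They stand as separate predictors, not as covariates for credibility.

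**The concern.** A patient who already feels better at week 3 has a reason to find the treatment logical and to expect to improve. The outcome counts that early gain. Credibility can therefore be associated with response because both reflect the same early change, with no further link between them. The other four hypothesised predictors (age, education, baseline severity, sickness-absence history) are fixed before treatment, so among the five the problem is specific to credibility.

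At stake is what may be concluded. Predictor Analysis aims to quantify each predictor's unique contribution. A univariate result cannot supply that for credibility, and the ablation supplies it only when the right symptom scores happen to be in the model.

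**Working it through.** **1. The plan's own figures.** It gives none for this test. The parent trial's sample size reproduces: 2(1.96 + 1.282)²/0.4² = 131.4, so 132 per arm; 132/0.9 = 146.7, so 147 per arm and 294 in total, against 300 stated. The check uses n = 300 × 0.9 = 270.

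**2. Structure.** Baseline - post = (baseline - week 3) + (week 3 - post). The first term has already happened when credibility is rated.

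**3. Assumptions (not in the document).** PSS-10 SDs 5.5, 6 and 6.5 and means 24, 21 and 17 at baseline, week 3 and post. The usual reliable-change form with SD 6 gives 1.96 × 6 × √2 × √(1 - 0.83) = 6.86, so a responder falls by 7 or more points, close to a median split. Tests are at 5%. Credibility correlates r with baseline - week 3 and has no other link to outcome.

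**4. Formulas.** A median split reduces a correlation by √(2/π) = 0.798, so a predictor with correlation c to total improvement has expected z = c × 0.798 × √270 = 13.11c.
- Credibility: c = r × corr(early change, total change).
- Week-3 PSS-10: c = corr(week 3, baseline - post).

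For correlations baseline-week 3 of 0.6, baseline-post of 0.4 and week 3-post of 0.55:
- SD of total change = √(30.25 + 42.25 - 28.6) = 6.63. SD of early change = √(30.25 + 36 - 39.6) = 5.16.
- Early with total: (30.25 - 14.3 - 19.8 + 21.45)/(5.16 × 6.63) = 0.515.
- Week 3 with total: (19.8 - 21.45)/(6 × 6.63) = -0.04.
- Credibility at r = 0.3: z = 13.11 × 0.3 × 0.515 = 2.03, so significant in Φ(2.03 - 1.96) = 53% of studies. At r = 0.2 and 0.4, z = 1.35 and 2.70, giving 27% and 77%. Simulation (1,500 studies per setting) gave 24%, 52% and 78%.

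Other assumed correlations, r = 0.3, same formulas:

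| Baseline-week 3 / baseline-post / week 3-post | Week 3 with total | Week-3 PSS-10 passes screen | Early with total | Credibility significant alone |
|---|---|---|---|---|
| 0.6 / 0.4 / 0.55 | -0.04 | 8% | 0.51 | 53% |
| 0.7 / 0.5 / 0.6 | -0.01 | 5% | 0.47 | 45% |
| 0.5 / 0.4 / 0.6 | -0.17 | 62% | 0.60 | 65% |
| 0.5 / 0.4 / 0.7 | -0.27 | 94% | 0.70 | 79% |

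**5. Ablation.** The plan attaches no test to it, so the proxy is whether credibility passes its screen and stays significant beside whichever PSS-10 scores passed theirs. Simulation over correlations of this kind at r = 0.3:
- Credibility significant alone: 47-80%.
- Week-3 PSS-10 enters: 6-94%.
- Credibility passes and stays significant: about 31% where week-3 PSS-10 rarely enters, down to 4% where it nearly always does.
- With both PSS-10 scores forced in: 3-6%.

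**6. A harder case for adjustment.** Here credibility follows true rather than observed early improvement (SD 6, mean change -7, early-total correlation 0.4 to 0.6, 600 studies per setting).

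| r | Unadjusted | Adjusted for baseline and week-3 PSS-10 |
|---|---|---|
| 0 | 4-5% | 3-6% |
| 0.2 | 14-30% | 4-6% |
| 0.3 | 26-51% | 6-10% |
| 0.4 | 45-81% | 6-13% |
| 0.5 | 60-92% | 7-19% |

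In this set-up baseline PSS-10 passed its own screen in only about half of the studies, so neither score can be taken for granted in the ablation model.

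**The case against.** **The hypothesis is about prediction, not cause.** The article says these variables will predict response. A week-3 rating that forecasts week-12 response does predict it, whatever drives the rating. This stands. A reader might infer that the 47-80% are false positives; for forecasting they are not, because in the simulation credibility truly is associated with the outcome. They are misleading only if read as a contribution beyond early change.

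**The timing is disclosed and deliberate.** Other week-3 measures are also listed as predictors. True, and no reason to drop credibility.

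**The ablation already addresses unique contribution.** In part. Where week-3 PSS-10 enters, credibility mostly drops out. A reader might infer that week-3 PSS-10 would usually fail the screen; that holds under some correlations and reverses under others, and the document gives none. The three burnout subscales and the insomnia score at week 3 may also enter and carry some early change; the simulations leave them out. What remains is that the result depends on which scores happen to pass.

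**Adjustment has its own cost.** If credibility produced the early gain, conditioning on week-3 PSS-10 removes a real effect. This stands, and it argues against making the adjusted coefficient the sole verdict.

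**Conclusion.** The point holds as a limit on interpretation. As planned, a significant univariate result for credibility supports forecasting from week 3 but not a contribution beyond symptom change to date, and the ablation does not reliably supply the missing comparison. The direction requires only that early improvement relates positively to both credibility and final response. The size rests wholly on assumed correlations and SDs.

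Two stronger readings are not supported: that a positive credibility finding would be wrong, and that adding the two PSS-10 scores restores the 5% level exactly. The second is true by construction when credibility is simulated from the observed scores; when it follows true early improvement, 4-19% remains for r of 0.2 to 0.5.

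This is a matter to consider. It touches one of five named hypotheses, and the primary comparison, test-set balanced accuracy, does not depend on it.

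**What to change.** - Report the credibility logistic regression twice: unadjusted, labelled as including improvement made by week 3, and adjusted for baseline and week-3 PSS-10.
- Claim a contribution beyond early improvement only if the adjusted coefficient supports it.
- Keep both PSS-10 scores in the ablation model whenever credibility is in it, whether or not they passed their own screens.
- Describe credibility as an early-treatment predictor, distinct from the pretreatment ones.

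The cost is one more regression on variables already in Table 1. The article reports that data had not been analysed for this study as of March 2025, so on that statement the change could still be prespecified. The adjusted estimate leaves out any effect of credibility that acted through early gain and may not remove all reverse influence, which is why both estimates should be shown.

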#### Cognitive Functioning

*Attention and processing speed* were measured using the Symbol Digit Modality Test. A test originally developed by Smith [58,59] that measures visual detection, attention, and processing speed. A key with 9 different symbols and matching numbers is shown on the upper part of the display. At the center one of these 9 symbols are shown and the task of the participant is to choose the corresponding number using the key as guidance. The test score is the number of correct entries in 90 seconds. Comparable substitution tasks are considered sensitive to treatment effects for patients with multiple sclerosis [60] and depression [61], and it has been used in patients with stress-related disorders [62].

*Executive functioning* was measured using the Verbal Fluency Test (FAS) Word Fluency Test and the Stroop test. FAS was first described by Spreen and Benton [63], and it measures spontaneous verbal fluency and selective attention and shifting. The participant is tasked with producing words beginning with a certain alphabet letter (F, A, and S). Names, numbers, or repeated words are not allowed. The test score is the number of correct words beginning with the letter. FAS and similar word fluency tasks have been shown to be impaired in patients with stress-related exhaustion [62].

The Stroop test, originally developed by Stroop [64] and described by Jensen and Rohwer [65], measures executive functioning, inhibition, as well as updating and processing speed [66]. The test has 2 parts, (1) 20 color words are presented (green, yellow, blue, or red) and they are colored congruent to their meaning (eg, the word red colored in red). In the bottom part of the display, the color words are displayed on 4 buttons. The task is to, as quickly and thoroughly as possible, click the correct button. (2) Twenty color words are presented but displayed in an incongruent color (eg, the word red colored in green). The task of the participant is to click the button containing the color of the word as quickly and thoroughly as possible. Test score is calculated as an index (number of correct answers in part 2 divided by average time in seconds from part 2) and for interference (average time in part one–average time in part one). Performance of Stroop in patients with stress-related disorders has been shown to be impaired in 2 studies [62,67], but not in others [68,69].

*Memory and learning* were assessed using the Consortium to Establish a Registry for Alzheimer’s Disease (CERAD) Word List Learning Test and Corsi block-tapping test forward. CERAD was originally developed for use with Alzheimer disease [70] but is similar to other word-list tasks used in this patient population. It measures verbal learning and episodic memory. In the learning part of the test, a word list containing 10 words is presented over 3 trials and the task after every trial is to recall the words from the list. For every presentation the order is mixed. In the delayed recall part of the test (trial 4) that occurs after 5 to 10 minutes, the participant is asked to recall the words. Test score for the learning time is number of correct words in trial 1 to 3, and in the delayed recall part, number of correct words in trial 4. Similar word-list tasks have been used previously to assess memory functioning in patients with stress-related disorders [62,69].

Corsi block-tapping test forward gives information about visual ability of attention, short-term memory and working memory [71]. It contains 2 parts, but in this test battery, only the first part of the test is used. Nine blocks are displayed, and the testing platform starts by lighting up a sequence of blocks. The task is to repeat the sequence of blocks that the platform has displayed. The task starts out easy with only 2 blocks, but the difficulty increases by adding a longer sequence of blocks until the participant enters the incorrect sequence twice at the same number of blocks. The test score is the maximum number of correct repeated blocks. A cross-sectional study comparing patients with stress-related disorders to a healthy normative group found impaired performance on this test [62].

